### Primary outcomes

Primary outcome will be the evaluation of changes in mean scores on CGI-BP-M between baseline and endpoint at the end of each phase of the study.

### Secondary outcomes

Secondary outcome will include the proportion of patients that achieve remission and response to each treatment at the end of each phase of the study, according to improvement in rating scales (HAM-D; MADRS; YMRS) and in clinical global impression specific for BD (CGI-BP-M) [15]. The CGI-BP-M is a clinician rating scale modified for Bipolar Disorder concerning to treatment response and consists of 3 sub-scales evaluating the severity of mania, depression and the whole disease symptoms.

Other outcome parameters are: safety and tolerability; quality of life and social adjustment; and cognitive impairment. These parameters will be evaluated comparing the endpoint measures of each phase with baseline. Safety and tolerability: according to the clinical evaluation of adverse effects and the measure on the UKU side effect rating scale [16]. UKU consists of 48 items clinician rated evaluating side effects in psychic, neurologic, autonomic and other domains. Quality of life and social adjustment: measure with the WHOQoL-BREF [17] and Social Adjustment Scale [18]. These instruments were translated and validated to Portuguese [19,20]. WHOQOL-BREF is a self report 26 items scale comprising 4 domains: physical, psychological, social and environment. The Social Adjustment Scale is a self report 54 questions instrument that measures instrumental and expressive role performance over the past two weeks. Cognitive impairment: neuropsychological tests (Wisconsin Card Sorting Test [21], Stroop Color Word Test [21], WASI - Wechsler Abbreviated Scale of Intelligence [22], Trail Making Test [21] and others), which are available in Portuguese. All investigators received appropriate training, and inter-rater reliability is periodically assessed.

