### Eligibility

Patients are recruited in the Institute of Psychiatry, of the Clinical Hospital of the University of Sao Paulo, School of Medicine. BD I patients according to the DSM-IV-TR [2], in depressive, manic,/hypomanic or mixed episode, aged 18 to 35 years are eligible. Patients with psychotic symptoms will be included and will not be stratified. Patients with co-morbid conditions are allowed to participate due to the study clinical reality approach ("more likely naturalistic study").

The patient or his/her legal representative should understand the nature of the study and sign the Informed Consent.

Eligible patients under pharmacological treatments proceed to a wash-out period according to the medication in use: 1 week for antidepressants (except fluoxetine and irreversible MAOI), antipsychotics (except clozapine), lithium, valproate, carbamazepine and other anticonvulsants; 2 weeks for irreversible MAOI; 4 weeks for fluoxetine and clozapine.

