### Study phases

Patients will be followed up for 8 weeks in phase I (acute treatment), 6 months in phase II (continuation treatment) and 12 months in phase III (maintenance treatment). Scales raters will be blind to the treatment. During phase II and III will continue only patients that achieve response, measured according to initial symptoms score in phase I. Patients with a new episode of any polarity detected in two consecutives visits will be discontinued from the study.

The definition of clinical course is defined according to Hirschfeld et al (2007) [12], Bauer et al (2007) [13] and Tohen et al (2009) [14]:

Non response: reduction ≤ 25% in severity of symptoms;

Partial response: improvement of symptoms between 26 and 49%;

Response: reduction ≥ 50% in severity of symptoms;

Remission: minimal or no symptoms for at least 1 week;

Sustained remission: at least 8 weeks of remission;

Relapse/recurrence: return of the criteria for the syndrome;

Roughening: return of symptoms in a subsyndromal level.

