### Planned Analyses

The primary analysis will be the evaluation of the mean scores on CGI-BP-M between baseline and endpoint in both groups. We will also evaluate differences comparing the two groups of treatment concerning total number of patients in full remission at the end of the study and the reason and time to drop out. Continuous data will be represented by mean and standard deviation (SD). Categorical variables will be described by table of frequencies. The results of all statistical comparisons of the treatment groups will be presented as a 2-sided p values rounded to 3 decimal places. The criterion for statistical significance in all comparisons will be p ≤ 0.05.

Continuous variables will be compared using repeated measures analysis of variance (ANOVA), with group of treatment and study phase as factors. Rates of response, remission and drop-outs will be compared between the two groups using a Pearson's X^2 ^test for categorical data. Dichotomous measures will also be compared using odds ratios and 95% confidence limits.

The correlation of clinical issues, quality of life, social adjustment and cognitive impairment will be evaluated by Pearson's correlation.

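### Tolerability, quality of life and cognition are judged on change to each phase's endpoint, so after phase I they describe responders only; the main contrast should be between arms at the end of phase I.

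*Protocol article*

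**What the plan says.** The Secondary outcomes section groups safety and tolerability, quality of life and social adjustment, and cognitive impairment, and gives one rule for all of them: "These parameters will be evaluated comparing the endpoint measures of each phase with baseline". Tolerability has two sources, "according to the clinical evaluation of adverse effects and the measure on the UKU side effect rating scale". The scale is described thus: "UKU consists of 48 items clinician rated evaluating side effects in psychic, neurologic, autonomic and other domains".

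Baseline is an episode of illness. Under Eligibility, patients "in depressive, manic,/hypomanic or mixed episode, aged 18 to 35 years are eligible", and "Eligible patients under pharmacological treatments proceed to a wash-out period according to the medication in use".

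Study phases sets who is observed later: "During phase II and III will continue only patients that achieve response, measured according to initial symptoms score in phase I". In addition, "Patients with a new episode of any polarity detected in two consecutives visits will be discontinued from the study".

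Planned Analyses compares continuous variables by repeated measures ANOVA with treatment group and study phase as factors. It compares drop-out rates between the groups by a Pearson chi-square test, and it lists among the group comparisons "total number of patients in full remission at the end of the study and the reason and time to drop out".

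**The concern.** Tolerability is half of the question in the trial's title. Three features of the stated rule weaken the answer.

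- **Selection after randomisation.** Phase II and III scores exist only for patients who responded in phase I and stayed. Patients who left for side effects are absent, and the two arms' survivors need not be comparable.
- **Possible spread to phase I.** In its conventional form, a repeated measures ANOVA with phase as a factor uses patients with a value at every phase. If it is run that way, the phase I contrast is also confined to patients who complete all phases.
- **A baseline taken in acute illness.** The UKU has a psychic domain, so recovery can lower the score whatever the drug does. Retesting can raise cognitive scores. Change within an arm therefore mixes recovery, practice and drug effect.

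At stake is a less well tolerated combination whose UKU scores look closer to the other arm's than they are, because the patients who tolerated it worst are no longer scored.

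**Working it through.** **1. The plan's own figure.** No figure is stated for tolerability. The sample size is for CGI-BP-M: 25 per group, 0.8 SD, two-sided 5%, 80% power.
- n per arm = 2(1.96 + 0.84)² / 0.8² = 24.5, rounded up to 25.
- Power at 25 per arm (normal approximation) = Φ(0.8·√(25/2) − 1.96) = Φ(0.87) = 0.807. By the noncentral t it is 0.791.

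The stated figure reproduces.

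**2. Effect of losing the worst-affected patients.** The article gives no UKU standard deviation and no drop-out rate, so all inputs here are assumptions. Let side-effect burden be normal with SD 1 and mean μ = 0 in one arm and μ = δ in the other. A patient leaves, unscored, if burden exceeds a threshold c. The mean among those scored is

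μ − φ(c − μ) / Φ(c − μ).

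Worked case, δ = 0.8, c = 1.5:
- Arm 1: 0 − 0.1295/0.9332 = −0.139, with 7% leaving.
- Arm 2: 0.8 − 0.3123/0.7580 = 0.388, with 24% leaving.
- Observed difference: 0.388 + 0.139 = 0.53, against a true 0.80.

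Simulation with 1,000,000 patients per arm agrees:

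| Threshold c | Leave, true 0.80 | Observed | Leave, true 0.50 | Observed |
|---|---|---|---|---|
| 2.0 | 2% v 12% | 0.64 | 2% v 7% | 0.42 |
| 1.5 | 7% v 24% | 0.53 | 7% v 16% | 0.35 |
| 1.0 | 16% v 42% | 0.41 | 16% v 31% | 0.28 |
| 0.5 | 31% v 62% | 0.31 | 31% v 50% | 0.21 |

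Scoring everyone who started returns 0.80 or 0.50.

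**3. Effect of recovery.** Suppose recovery lowers UKU by r₁ in arm 1 and r₂ in arm 2. Each arm's change falls by its own r, and the difference between arms becomes δ − (r₂ − r₁). With r₁ = r₂ = 0.5 SD, the difference stays at 0.80 (or 0.50). Bias arises only when r₁ ≠ r₂, that is, when the combinations differ in efficacy, which is what the primary outcome tests.

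**4. What the drop-out comparison can show.** Take 5/25 v 1/25 stopping for side effects (assumed).
- Difference: 20% − 4% = 16 percentage points.
- Standard error: √(0.2·0.8/25 + 0.04·0.96/25) = 0.089.
- 95% CI: 16 ± 17.5, so −1.5 to 33.5 points.

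The planned comparison of reasons for drop-out would show this contrast, but imprecisely. Power at 25 per arm is

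Φ{(|p₂ − p₁| − 1.96·√(2p̄(1 − p̄)/25)) / √([p₁(1 − p₁) + p₂(1 − p₂)]/25)},

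where p̄ is the mean of the two rates. It is 0.42 for 10% v 30%, 0.70 for 10% v 40% and 0.90 for 10% v 50% (assumed rates).

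**5. Change score or baseline adjustment.** With equal variances at baseline and endpoint and correlation ρ between them, a change score has variance proportional to 2(1 − ρ) and a baseline-adjusted comparison to 1 − ρ². The ratio of adjusted to change is (1 + ρ)/2, which is below 1 for any ρ < 1. Adjustment is therefore at least as precise and uses a baseline that is already measured.

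**The case against.** The best defence is that Planned Analyses already answers much of this. It has treatment group as a factor, so the contrast is between arms and common recovery or practice effects cancel, as step 3 shows. It compares reason and time to drop out between the groups, which is where patients who could not tolerate treatment would appear. Tolerability also rests on clinical evaluation of adverse effects, not on the UKU alone. Taking responders forward is a design choice, and these are non-primary outcomes in a study that calls itself exploratory.

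Most of that stands, and it rules out some stronger readings:

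- A reader might infer that intolerant patients vanish from the trial's results. They do not, because the drop-out comparison retains them.
- A reader might infer that patients who stop before week 8 have no phase I endpoint. The article does not say so. The term could mean the last observation, and handling of missing data may be set out in a fuller document.
- A reader might infer that illness improvement invalidates the comparison of the arms. It does so only if improvement differs by arm.

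The defence does not reach three things. The phase II and III scores are restricted to responders however the endpoint is defined. The chi-square test is on drop-outs as a whole, and stopping for adverse effects is not named as a tolerability outcome. Finally, clinical evaluation of adverse effects falls under the same endpoint-versus-baseline sentence as the UKU.

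**Conclusion.** The concern holds in a limited form. The rule in Secondary outcomes is a poor main comparison for tolerability, quality of life and cognition. Its later-phase scores are selected by outcome after randomisation, and the named ANOVA could carry that selection back to phase I. Its within-arm change cannot separate drug effect from recovery.

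Selection in phases II and III follows directly from the responder rule. Restriction of the phase I contrast is conditional: it depends on how the ANOVA is run and on whether early leavers have a rating.

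The sizes (0.80 SD falling to 0.64–0.31, and 0.50 falling to 0.42–0.21) are illustrations. They assume normal burden, a common leaving threshold and no score for those who leave. They show direction and possible scale, and are not estimates for this trial. The point affects the reading of secondary outcomes, not the primary one, and should be put right before analysis.

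**What to change.** Replace the endpoint-versus-baseline sentence with three statements.

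1. The main comparison for UKU, quality of life, social adjustment and cognition is the difference between arms at the end of phase I (week 8), adjusted for the baseline value, in all treated patients. For early leavers, use the last available rating where one exists.
2. The proportion stopping for adverse effects, by arm, with difference and 95% CI, is a tolerability outcome to be read alongside the UKU.
3. Change within an arm, and all phase II and III scores, are descriptive, and the later scores are labelled as being in responders only.

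A worst post-baseline UKU score is an optional addition, possible only if the UKU is rated between baseline and the phase endpoint. The article does not show such ratings, or an exit visit.

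The cost is wording and slightly more analysis. Two limits remain. The last rating of an early leaver reflects shorter exposure, so the scores of patients who reached week 8 should be shown beside it. And adjusting for baseline does not remove recovery that differs between arms, so the UKU psychic domain should be read with the efficacy result in view.

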### Planned Analyses

The primary analysis will be the evaluation of the mean scores on CGI-BP-M between baseline and endpoint in both groups. We will also evaluate differences comparing the two groups of treatment concerning total number of patients in full remission at the end of the study and the reason and time to drop out. Continuous data will be represented by mean and standard deviation (SD). Categorical variables will be described by table of frequencies. The results of all statistical comparisons of the treatment groups will be presented as a 2-sided p values rounded to 3 decimal places. The criterion for statistical significance in all comparisons will be p ≤ 0.05.

Continuous variables will be compared using repeated measures analysis of variance (ANOVA), with group of treatment and study phase as factors. Rates of response, remission and drop-outs will be compared between the two groups using a Pearson's X^2 ^test for categorical data. Dichotomous measures will also be compared using odds ratios and 95% confidence limits.

The correlation of clinical issues, quality of life, social adjustment and cognitive impairment will be evaluated by Pearson's correlation.

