### Sample Size and Randomization

Sample size was calculated comparing the mean difference in CGI-BP-M scores between baseline and endpoint for the two groups. If we compare this using a Student's t test we find that with 50 patients (25 in each group) we achieve 80% power (in a 5% of significance level test) to detect a difference of 0.8 standard deviation, which can be considered a large effect size [11]. Due to the exploratory nature of this study and the difficulties of compliance in a long term trial, this seems to be an acceptable value.

The random allocation sequence was computer generated by a biostatistician. Patients were enrolled by clinicians who have their code revealed by the research monitor when assigned to interventions. Blinding the outcome assessor is done keeping their evaluation independent to the clinician.

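### A single p ≤ 0.05 significance rule covers every secondary and other comparison, with no order or adjustment, and the study's stated exploratory nature is not carried into that rule

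*Protocol article*

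**What the plan says.** Under Planned Analyses, the protocol article names the primary analysis (CGI-BP-M, baseline to endpoint) and then sets two rules for everything. On presentation: "The results of all statistical comparisons of the treatment groups will be presented as a 2-sided p values rounded to 3 decimal places". On interpretation: "The criterion for statistical significance in all comparisons will be p ≤ 0.05". Continuous variables go into a repeated-measures ANOVA with treatment group and study phase as factors. Response, remission and drop-out rates are compared by Pearson chi-square, with odds ratios and 95% confidence limits for dichotomous measures. Clinical, quality-of-life, social-adjustment and cognitive variables are also to be correlated with one another.

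The section on secondary outcomes opens as follows: "Secondary outcome will include the proportion of patients that achieve remission and response to each treatment at the end of each phase of the study". These are judged on HAM-D, MADRS, YMRS and CGI-BP-M. A further group, called other outcome parameters, covers tolerability (UKU), quality of life (WHOQoL-BREF, four domains), social adjustment, and cognition (four named tests in an open-ended list). Of this group it says: "These parameters will be evaluated comparing the endpoint measures of each phase with baseline".

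Under Sample Size and Randomization, the modest size is accepted with the words "Due to the exploratory nature of this study and the difficulties of compliance in a long term trial". That is the only place where the study is described as exploratory.

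**The concern.** The article does more than leave multiplicity unmentioned. It states a working criterion that gives a secondary result on one scale at one phase end the same standing as the primary result. No secondary comparison is put first, none is adjusted, and none is labelled exploratory where the criterion is stated.

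The trial has 25 patients per group and is sized for a large effect, so a primary result short of significance is quite possible. A p value of 0.04 on one scale at one phase end could then be reported, within the plan, as a statistically significant difference between the two combinations.

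Remission adds some freedom. Secondary outcomes places it at the end of each phase, while Planned Analyses names full remission at the end of the study. Several versions of the comparison therefore exist under the same criterion.

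**Working it through.** **1. The plan's own figure.** The article says "with 50 patients (25 in each group) we achieve 80% power (in a 5% of significance level test" and "to detect a difference of 0.8 standard deviation, which can be considered a large effect size". The normal approximation gives n per group = 2 × (1.960 + 0.842)² / 0.8² = 24.5, rounded up to 25, with power 80.7% at 25. The exact noncentral t gives 79.1%. The stated design reproduces as a two-sided 5% test of one contrast. The calculation makes no allowance for further tests.

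**2. Counting the tests.**
- Response and remission as one composite each: 2 outcomes × 3 phase ends = 6.
- Response and remission on each scale: 2 × 4 scales × 3 phase ends = 24. This is a ceiling.
- Other measures: 1 (UKU) + 4 (WHOQoL-BREF domains) + 1 (Social Adjustment Scale) + 4 (named cognitive tests) = 10. Phase is a factor in the planned ANOVA, so the count is one model per measure: 10 tests, not 10 × 3.
- Composite response and remission plus the ANOVAs: 6 + 10 = 16.

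Not counted: unnamed cognitive tests, drop-out comparisons, the Pearson correlations, and separate group-by-phase terms in the ANOVAs.

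**3. Chance of at least one p ≤ 0.05 when nothing differs.** For k independent tests this is 1 − 0.95^k; for example, 1 − 0.95^6 = 26%. For correlated tests I used normal test statistics with a common correlation r and counted any |z| above 1.96. The documents give no correlations, so r is an assumption.

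| Tests | r = 0 | r = 0.5 | r = 0.8 |
|---|---|---|---|
| 6 (composite response and remission) | 26% | 21% | 14% |
| 10 (ANOVAs) | 40% | 29% | 17% |
| 16 (6 + 10) | 56% | 37% | 21% |
| 24 (four scales separately) | 71% | 46% | 24% |

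Adding the ten ANOVAs to the ceiling of 24 gives 34 tests: 83%, 53% and 27% in the same order.

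**4. Reading the table.** Every cell is well above 5%; the smallest is 14%. At r = 0.5 the chance stays below one half for 6 to 24 tests. It passes one half only if the ceiling count is taken and the ANOVAs are added.

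**The case against.** The best case on the other side has five parts.

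*The study is called exploratory.* This is partly right. The subject of that phrase is the study, so it cannot be said that no exploratory label exists. But it serves there to justify the sample size, and the later rule covers every comparison without qualification.

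*Tiers already exist.* Tolerability, quality of life, social adjustment and cognition are set apart as other parameters, and full remission at the end of the study is mentioned straight after the primary analysis, which may be meant to give it prominence. Both observations stand. Neither changes the criterion applied to these outcomes, and the remission time point still differs between the two sections.

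*The analysis plan may deal with this.* Ordering and adjustment of secondary tests are commonly left to it, and their absence here is not the point. The point is the rule that is stated, which an analysis plan would have to override.

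*Nothing says that a secondary result would count as trial success.* This is correct, and it is the main reason why the point is minor.

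*Part of the remedy is already planned.* Odds ratios with 95% confidence limits are specified for dichotomous measures. That helps, but it leaves the significance claim in place.

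A reader might also infer that most significant secondary results would be chance findings. That does not follow. The figures above give the chance of at least one false positive when nothing differs. The share of significant results that are false depends also on how many true differences exist and on power for them, and the documents give neither.

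**Conclusion.** The concern holds as a minor point about the stated rule. If it is followed as written, and if there are no true differences, the chance of at least one nominally significant secondary or other result is about 21% for 6 tests, 29% for the ten ANOVAs, 37% for 16 tests and 46% for 24 tests at an assumed correlation of 0.5. Over 6 to 24 tests and correlations from 0.8 to 0, the range is 14% to 71%.

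Two stronger readings are not supported. A chance secondary finding cannot simply be called likely: that depends on a test count and a correlation that the document does not fix. Nor does the plan break a promised overall error rate: its 5% is a criterion for each comparison, and no family-wise rate is stated. The conclusion that survives any reasonable count and correlation is that the chance is well above 5%, while the rule treats every such result as significant.

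**What to change.** In Planned Analyses, limit the p ≤ 0.05 significance criterion to the primary CGI-BP-M analysis. State that secondary outcomes, other outcome parameters and the correlations are exploratory and are reported as estimates with 95% confidence intervals, without a claim of significance. Reconcile the remission time point between Secondary outcomes (end of each phase) and Planned Analyses (end of the study).

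I would not add a key secondary outcome tested only after a significant primary result. Primary outcomes defines the primary at the end of each of three phases, so a single primary contrast would have to be named first.

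The change takes a few sentences and no extra data. Its cost is that nominal secondary p values can no longer be claimed as significant.

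### The trial is powered on a t test of CGI-BP-M change but analysed by a group-and-phase ANOVA with no named deciding contrast and no baseline covariate; one baseline-adjusted contrast per phase end would align the two and gain precision

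*Protocol article*

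**What the plan says.** **Sizing.** Under Sample Size and Randomization, the quantity compared is change from baseline: "Sample size was calculated comparing the mean difference in CGI-BP-M scores between baseline and endpoint for the two groups". The test is named ("If we compare this using a Student's t test"), and the claimed power is 80% for 25 patients per arm at the 5% level. The target effect is 0.8 SD, which the article calls large. No covariate enters this calculation.

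**Outcome.** Primary outcomes sets the change in mean CGI-BP-M from baseline at the close of each of the three phases: 8 weeks, then 6 months, then 12 months.

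**Analysis.** Planned Analyses describes the primary analysis as mean CGI-BP-M between baseline and endpoint in the two groups. It then states: "Continuous variables will be compared using repeated measures analysis of variance (ANOVA), with group of treatment and study phase as factors". It names no interaction, no deciding contrast and no covariate, and does not say whether baseline is a level of the phase factor.

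**Reporting.** Planned Analyses describes continuous data by mean and SD, gives p values for the group comparisons ("The results of all statistical comparisons of the treatment groups will be presented as a 2-sided p values rounded to 3 decimal places"), and adds odds ratios with 95% confidence limits for dichotomous measures. No interval is mentioned for a difference in means.

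**The concern.** The power statement and the analysis model concern different tests unless the ANOVA is read in one particular way. A group-and-phase ANOVA offers at least two candidates for the treatment test:

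- the group effect, averaged over occasions;
- the group-by-phase interaction.

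They answer different questions and have different power. If neither is named, the choice stays open until the results are seen, and the stated 80% cannot be attached to either.

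The second issue is precision. Baseline CGI-BP-M must be collected, because the outcome is a change from it. Subtracting baseline forces a slope of 1 on it; using it as a covariate lets the data set the slope. In a trial of 50 patients, sized only for what the article itself calls a large effect, that difference is worth having. A p value without an interval for the mean difference would also leave a non-significant result hard to read.

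**Working it through.** **Inputs from the article.** n = 25 per arm, difference 0.8 SD, alpha 0.05 (Sample Size and Randomization); two-sided (Planned Analyses). The 0.8 is read as SDs of the change score, because change is what is compared.

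**Inputs assumed.** Baseline-endpoint correlation rho = 0.3, 0.5, 0.7, with equal variances and equal correlations across occasions. The article gives none of these.

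**1. The plan's own figure.** The noncentrality is 0.8 × √(25/2) = 2.828 on 48 df. Exact power is 79.1%; the normal approximation gives 80.7%. The stated 80% reproduces.

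**2. ANOVA with two occasions (baseline, endpoint).** The group-by-time interaction has noncentrality 2.828² = 8 on 1 and 48 df. Its F is the square of the change-score t (confirmed numerically on simulated data), so power is again 79.1%. There is no mismatch in this case.

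**3. ANOVA with four occasions (baseline and three phase ends).** Let p be the effect at each occasion as a fraction of the full 0.8 SD-of-change effect. The SD of change is √(2(1 − rho)) in units of the raw SD, so the interaction noncentrality is

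(n/2) × 0.8² × 2(1 − rho) × Σ(p − p̄)² / (1 − rho) = 16 × Σ(p − p̄)²,

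and rho cancels. The test has 3 and 3 × 48 = 144 df.

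| Effect profile p | Σ(p − p̄)² | Noncentrality | Power |
|---|---|---|---|
| 0, 1, 1, 1 (constant after baseline) | 0.75 | 12.0 | 82.9% |
| 0, 0, 0, 1 (last phase only) | 0.75 | 12.0 | 82.9% |
| 0, 1/3, 2/3, 1 (linear build-up) | 0.556 | 8.9 | 69.2% |

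This is a different test from the powered one, and its power depends on the time course. Other profiles could fall outside this range.

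**4. Baseline as covariate.** With equal variances, the variance of the change-score comparison is proportional to 2(1 − rho) and that of ANCOVA to 1 − rho². The ratio is (1 − rho²) / [2(1 − rho)] = (1 + rho)/2, below 1 for any rho below 1. The standardised effect becomes 0.8/√((1 + rho)/2), on 47 df.

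| rho | Variance ratio | Standardised effect | Noncentrality | Power at 25 per arm | n per arm for 80% | Detectable difference at 80% (SD of change) |
|---|---|---|---|---|---|---|
| Unadjusted | 1 | 0.800 | 2.828 | 79.1% | 26 | about 0.8 |
| 0.3 | 0.65 | 0.992 | 3.508 | 93.0% | 17 | 0.65 |
| 0.5 | 0.75 | 0.924 | 3.266 | 89.2% | 20 | 0.70 |
| 0.7 | 0.85 | 0.868 | 3.068 | 85.2% | 22 | 0.75 |

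**5. Index episode as an extra term (2 df).** If it explains nothing, power changes by 0.1 point or less. If it explained 10% of the residual variance, power would be 95.1%, 92.0% and 88.6% at the three correlations. That 10% is purely illustrative.

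**6. Interval width.** The unadjusted 95% half-width is t(0.975, 48) × √(2/25) = 2.011 × 0.283 = 0.57 SD of change. A non-significant result could therefore be compatible with a sizeable difference, which a p value alone would not show.

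**The case against.** **A condensed article may leave covariates to a fuller document, and an unadjusted analysis is valid under randomisation.** Both statements are correct. A missing covariate alone would not be a finding, and ANCOVA here improves precision without correcting a bias. What remains is that the article does state the test it powered and the factors of its model, and these do not match unless the ANOVA has two occasions and the interaction decides.

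**If baseline is a phase level, baseline is already used.** It is, by subtraction. What is unused is the further gain from estimating its slope.

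**The gain depends on an unknown correlation.** Its size does. Its direction, with equal variances, does not.

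Four stronger readings are tempting, and the article does not support them:

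- *The planned test has very low power.* With two occasions the group main effect would have 53%, 36% and 21% power at rho 0.3, 0.5 and 0.7. With four occasions it would range from about 9% to 95%. Nothing makes that effect decisive, and an outcome defined as change points to the interaction.
- *Results will be given only as p values.* Means, SDs, and odds ratios with confidence limits are also planned. Only the interval for continuous differences goes unmentioned.
- *Randomisation ignored index episode.* The sentence on stratification, "Patients with psychotic symptoms will be included and will not be stratified", concerns psychotic symptoms. The article is silent on stratifying by episode, and no figure shows that episode predicts outcome. The Background's remarks on which presentations suit which drug describe effect modification, which a main-effect term would not address.
- *The primary analysis should move to week 8.* That would replace the stated primary outcome, which covers all three phase ends, in a trial whose stated focus is preventing relapse and recurrence. It would be a change of question and is not part of this point.

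**Conclusion.** The point holds as an inexpensive improvement. The powered test and the analysis model agree only in the two-occasion reading with the interaction as the deciding test. With the three phase ends that define the primary outcome, the 3-df interaction has about 69% to 83% power over the profiles tried, and no deciding contrast is named. Baseline adjustment cuts the variance of the change comparison by 35%, 25% or 15% at rho 0.3, 0.5 or 0.7, and lifts power from 79% to about 93%, 89% or 85%.

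These figures assume equal variances, the listed correlations, a 5% two-sided test for each single comparison, and all 25 patients per arm observed. The last holds at best for phase I: the Study phases section lets only responders continue, so later comparisons have fewer patients, selected after randomisation. Baseline adjustment does not repair that.

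**What to change.** In Planned Analyses:

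1. For each phase-end comparison already listed under Primary outcomes, estimate the between-group difference in CGI-BP-M with treatment as the factor and baseline CGI-BP-M as covariate, either by ANCOVA or as the corresponding contrast of a baseline-adjusted mixed model.
2. Name that contrast as the deciding test, in place of an unspecified effect from the group-and-phase ANOVA.
3. Report the adjusted difference with its 95% confidence interval beside the p value, as is already planned for dichotomous measures, and do the same for the other continuous outcomes.
4. Optionally add index episode (manic/hypomanic, depressive, mixed) as a covariate, stating that any gain is assumed.

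In Sample Size and Randomization, restate power for the named contrast, with the assumed correlation and the number of patients expected at that phase end.

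The primary time points do not change. The cost is a wording change and one degree of freedom, or three with index episode. No new data on CGI-BP-M are needed, and the article describes the trial as still in progress.
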